#### Secondary objectives

The secondary objectives of the MicUTI trial are to compare the intervention and control practices with regard to the following endpoints:

Total antibiotic use: number of antibiotic prescriptions per patient with UTI within 28 days.Defined daily doses of the prescribed antibiotics per patient with UTI within 28 days.Inappropriate antibiotic use: the percentage of patients with symptoms of UTI who were prescribed antibiotics among those with negative urine culture findings.Number of immediate and delayed antibiotic prescriptions for uUTI at the initial consultation.Number of early relapses of UTI (days 0–14).Number of recurrent UTIs (days 15–28).Number of upper UTIs within 28 days.Number of consultations due to UTI (or symptoms of UTI) within 28 days.Time to complete symptom resolution is defined as a maximum of 1 point in each of the Urinary Tract Infection-Symptom and Impairment Questionnaire (UTI-SIQ-8) items.^27^
Total symptom burden on days 0–7 (area under the curve of the UTI-SIQ-8 total symptom score).Diagnostic accuracy of microscopy with or without concomitant dipstick test compared with the reference standard test (urine culture).

A further objective of this study is to evaluate the feasibility and acceptability of POC-microscopy to detect bacteria in urine and the training sessions addressed to medical assistants in the intervention arm practices.

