**Methods and analysis:**

This is an open-label two-arm parallel cluster-randomised controlled pilot trial. 20 general practices affiliated with the Bavarian Practice-Based Research Network (BayFoNet) in Germany were randomly assigned to deliver patient management based on POCTs or to provide usual care. POCTs consist of phase-contrast microscopy to detect bacteria and urinary dipsticks to detect erythrocytes in urine samples. In both arms, urine samples will be obtained at presentation for POCTs (intervention arm only) and microbiological analysis. Women will be followed-up for 28 days from enrolment using self-reported symptom diaries, telephone follow-up and a review of the electronic medical record. Primary outcomes are feasibility of patient enrolment and retention rates per site, which will be summarised by means and SDs, with corresponding confidence and prediction intervals. Secondary outcomes include antibiotic use for UTI at day 28, time to symptom resolution, symptom burden, number of recurrent and upper UTIs and re-consultations and diagnostic accuracy of POCTs versus urine culture as the reference standard. These outcomes will be explored at cluster-levels and individual-levels using descriptive statistics, two-sample hypothesis tests and mixed effects models or generalised estimation equations.

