#### Point-of-care test guided treatment algorithm

Based on the prognostic and moderating effects on treatment outcomes of erythrocytes and bacteria in urine,^13^ GPs will be encouraged to apply the following treatment algorithm (figure 1) to consenting women, taking their preferences into account:

If POCTs are positive for bacteria by microscopy and/or for erythrocytes by dipsticks, the GP issues, at their own clinical judgement, a delayed or immediate prescription for an antibiotic. In the MicUTI intervention, a delayed prescription can be issued by GPs, at their discretion, in either way: the prescription is handed out to the patient with the advice to redeem it only if symptoms do not improve or worsen in 48 hours, or it is withheld in the GP practice. It can be handed out if the patient presents again with issues.If POCTs are negative for bacteria and erythrocytes, the GP advises for self-help remedies according to national guidelines and to do without antibiotics.^33 34^

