##### Follow-up

Follow-up data will be collected through a self-directed patient diary, follow-up telephone calls on day 28 from inclusion and follow-up in the GP practice in case of reconsultation. In addition, an electronic medical records (EMR) review will also be performed to double-check for missing follow-up data.

**Patient diary:** Women will be asked to rate their daily symptoms and impairment due to UTI on a scale from 1 (no symptoms/impairment at all) to 5 (very strong symptoms/impairment) and to write down the antibiotics taken in a diary for at least 7 days (or up to 14 days if symptoms last longer).^27^ Enough space in the diary is left for women to take extra notes. They will be asked to return the completed diary to their GP practice using a pre-paid envelope or in person. Research nurses at the FAU and the LMU will perform telephone calls on days 2–4 from inclusion to remind enrolled women to fill out and return the diary.

**Follow-up telephone calls:** Calls will be performed by research nurses at the FAU and the LMU on day 28 from inclusion to collect data on symptoms, antibiotic use due to UTI, recurrences and reconsultations with UTI symptoms.

**Follow-up in the GP practice:** Every time a woman reconsults for UTI within 28 days, the GP records clinical features, management decisions and antibiotics prescribed on follow-up paper-based CRFs.

**Electronic medical records review:** Researchers from the UKW and the FAU will perform outreach visits at the end of the patient recruitment (6 months) in each of the study sites. Paper-based CRFs will be collected, and data will be controlled for completeness. To double-check data entries for accuracy and completeness, EMRs will be enquired on reconsultations with UTI symptoms, recurrences, antibiotics prescribed due to UTI and upper UTI until day 28 from inclusion.

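### A count of prescriptions is labelled total antibiotic use, so delayed prescriptions never redeemed count as use, and intake data that are collected enter no listed endpoint

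*Protocol article*

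**What the plan says.** The first endpoint under Secondary objectives is "Total antibiotic use: number of antibiotic prescriptions per patient with UTI within 28 days". The next is "Defined daily doses of the prescribed antibiotics per patient with UTI within 28 days". The inappropriate-use endpoint also rests on prescribing: it takes patients "who were prescribed antibiotics among those with negative urine culture findings". A further endpoint is "Number of immediate and delayed antibiotic prescriptions for uUTI at the initial consultation", which covers the index visit only.

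Under the heading on the point-of-care test guided treatment algorithm, if either test is positive "the GP issues, at their own clinical judgement, a delayed or immediate prescription for an antibiotic". A delayed prescription takes one of two forms: it is "handed out to the patient with the advice to redeem it only if symptoms do not improve or worsen in 48 hours", or it stays at the practice and is released if the woman comes back. The text treats both forms as issued.

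The Follow-up section collects intake separately. Women are asked "to write down the antibiotics taken in a diary for at least 7 days", extended to 14 days if symptoms persist, and the day-28 call asks about antibiotic use for UTI. The abstract names the outcome "antibiotic use for UTI at day 28" and gives the aim as finding out whether the strategy can safely lower antibiotic use.

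**The concern.** Prescribing and taking an antibiotic are different events, and the protocol collects data on both. A delayed prescription is the case where they part: it is issued on condition, and the condition may not arise. By labelling the prescription count as use, the endpoint list counts unredeemed prescriptions as antibiotics consumed. This departs from the stated aim, from the abstract and from the data gathered at follow-up. It is also unclear whether a prescription kept at the practice and never collected counts.

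The stake is planning. The pilot is meant to inform the sample size of a full trial and to give initial data on antibiotic use, and ICCs are to be calculated for the secondary endpoints for that purpose. If the later trial is about use, effect sizes and ICCs derived from prescriptions may not carry over. The index-visit count shows how many prescriptions were delayed, but not how many were redeemed, so a reader could not correct the estimate from the listed endpoints.

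**Working it through.** **Plan's own figure.** There is none for this endpoint: no antibiotic rate, effect size or power is stated. The only design calculation concerns complete follow-up (200 women, 75% complete, 95% CI narrower than 13% with probability 0.90). Ignoring clustering, an exact binomial interval gives 0.889, close to the stated 0.90. It does not bear on this point.

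**Inputs for an illustration.**
- Control share prescribed, p_C = 0.95. The Introduction says up to 95% of women receive antibiotics; taking this as the control rate is an assumption.
- Intervention share prescribed, p_T = 0.75: assumed.
- Share of prescriptions that are delayed, d, per arm: not in the document; 0 to 40% assumed.
- Share of delayed prescriptions redeemed, r: not in the document; 30% to 70% assumed, the same in both arms.

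The illustration uses the share of women with any prescription. The endpoint is a count per patient, so repeat prescriptions are left out.

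**Formulas.** Share using antibiotics in an arm: U = p × [1 − d(1 − r)]. Prescription difference minus use difference: p_C·d_C(1 − r) − p_T·d_T(1 − r). The second expression is zero when nothing is delayed (d = 0 in both arms) or everything is redeemed (r = 1).

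**Example, only the intervention arm delays, d_T = 0.40, r = 0.30.** U_T = 0.75 × (1 − 0.40 × 0.70) = 0.54 and U_C = 0.95. The use difference is 0.41, against a prescription difference of 0.95 − 0.75 = 0.20, so the prescription count understates the reduction by 21 points.

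**Example, control delays more, d_C = 0.40, d_T = 0.20, r = 0.30.** U_C = 0.95 × 0.72 = 0.684 and U_T = 0.75 × 0.86 = 0.645. The use difference is 0.039, so the prescription count overstates the reduction by 16.1 points.

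**Range over r = 0.30 to 0.70, prescription difference 20 points throughout:**

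| Delayed share (intervention / control) | Use difference, points | Prescription minus use, points | Risk ratio for use (0.79 on prescriptions) | n per arm on use (49 on prescriptions) |
|---|---|---|---|---|
| 0 / 0 | 20 | 0 | 0.79 | 49 |
| 20–40% / 0 | 24.5 to 41 | −4.5 to −21 | 0.74 to 0.57 | 37 to 17 |
| 40% / 40% | 14.4 to 17.6 | +5.6 to +2.4 | 0.79 | 179 to 95 |
| 20% / 40% | 3.9 to 13.1 | +16.1 to +6.9 | 0.94 to 0.84 | 2300 to 161 |

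The n per arm is for two proportions, two-sided 5%, 80% power, without clustering. It shows only how far planning could move.

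**Sensitivity to p_T.** With p_T = 0.85 the prescription difference is 10 points. The use difference is then 15.1 to 33.8 points if only the intervention arm delays 20–40%, and −4.7 to +3.7 points if control delays 40% and intervention 20%.

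**ICC.** No figure can be given. An ICC for prescriptions and one for intake describe different variables, and the document offers nothing from which to convert one into the other.

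**The case against.** Five points can be made for the plan.

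- **The endpoint is secondary.** The primary endpoints are recruitment and retention, the effect analyses are exploratory, and the article says the trial is not powered for effects. This stands: nothing here touches the feasibility decision, and the endpoint should not be called the trial's key estimate.
- **No bias is demonstrated.** A reader might infer that counting unredeemed prescriptions inflates use mainly in the intervention arm and so hides a benefit. The document does not support that direction. Delayed prescriptions are listed among endpoints compared between both arms, usual care does not exclude them, and the table shows that the sign can reverse. This stands.
- **A prescription count is a legitimate measure.** Prescribing is what the intervention acts on directly. It is recorded on case report forms and checked against the electronic medical records, so it does not depend on self-report. This stands as a reason to keep the endpoint, not as a reason to call it use.
- **Counting rules may sit in an analysis plan that is not shown.** This is fair for the handling of prescriptions kept at the practice. It does not cover the definition, which the article itself states in terms of prescriptions while the abstract speaks of use.
- **The denominator is not shown to be wrong.** A reader might take the words about patients with UTI to mean culture-confirmed infection, dropping test-negative women. That is strained: women are enrolled on symptoms, no confirmed-infection analysis set is defined, and where culture restricts a denominator the list says so.

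**Conclusion.** The point holds as a mismatch between label and definition with practical consequences. The endpoint called total antibiotic use measures prescriptions issued, the intervention algorithm allows prescriptions that may not be redeemed, and the intake data collected are not tied to any listed endpoint. The estimated effect on use, and the ICC handed to the confirmatory trial, can be off in either direction.

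The size is unknown. Under the assumed 95% against 75% prescribed and 30–70% redemption, the prescription difference falls short of the use difference by up to 21 points or exceeds it by up to 16.1 points, depending on which arm delays more. These figures follow from assumptions and are not estimates for this trial. A correction is worth making because it is cheap and lets the pilot answer its stated question. It does not affect the feasibility decision, and it implies no change to the treatment algorithm.

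**What to change.** 1. Rename the existing count and the defined-daily-dose endpoint as antibiotics prescribed. State that delayed prescriptions, whether handed out or kept at the practice, are counted the same way in both arms. The inappropriate-use percentage also rests on prescribing, so its label can be aligned at the same time.
2. Define antibiotic use as antibiotics for UTI actually taken by day 28 (any use, and number of courses where recorded), from the diary plus the day-28 call, over all enrolled women.
3. Where self-report is missing, use prescriptions from the case report forms and electronic medical records as a sensitivity analysis.
4. Report the ICC for both prescribing and use, so that the later trial can plan on whichever it adopts.

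The cost is mainly endpoint wording, because the diary and call are already in place. The article does not say that dose or duration taken is recorded, so defined daily doses should stay on the prescribed basis. The drawback is quality: intake is unblinded self-report, rests on a single call once the diary ends at 7 to 14 days, and is exposed to loss to follow-up (the sample size section assumes 75% complete). That is why the prescription endpoints should stay alongside it.

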**Trial registration number:**

ClinicalTrials.gov NCT05667207.

Strengths and limitations of this studyThis study will inform the design and conduct of future confirmatory randomised controlled trials (RCTs) to evaluate the effects of a point-of-care test-guided management strategy on the use of antibiotics in women with suspected uncomplicated urinary tract infection in primary care settings.The open-label cluster-RCT design implies that participants cannot be identified before randomisation, thus, post-randomisation recruitment may represent a source of selection bias.The execution and interpretation of microscopy test results may potentially differ across medical assistants, affecting diagnostic accuracy measurements and treatment outcomes. This will be counteracted by providing all intervention practices with standardised ad hoc competency-based training.

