### Randomisation of study sites

General practices participating in the trial (hereafter: study sites) will be asked to provide the number of consulting patients over the last year to determine practice size. Study sites of larger size are foreseeably able to recruit more patients for the duration of the trial, so that practice size will be balanced between the two arms (each with 10 practices) using minimisation.^29^ The minimisation algorithm is centrally programmed in Python by the study statistician. To mask the trial statistician (GB) to intervention/control assignments, the minimisation algorithm will be executed by the trial’s statistical consultant based at the Technical University of Munich (AH), who is not involved in the conduction of the trial. Intervention/control assignments of practices will be communicated to the UKW and the FAU, who then will communicate their allocation to the study sites. To minimise selection bias, study sites were identified for inclusion in the trial prior to randomisation.

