### Patient recruitment/enrolment

#### Identification of women eligible for inclusion

At presentation, at all study sites, medical assistants will consecutively approach all adult women presenting with two or more symptoms suggestive of acute uUTI (dysuria, frequency, urgency, nocturia, lower abdominal pain) to identify trial participants. To ensure consecutive enrolment and control for selection bias, all potential participants will be approached and listed in paper-based anonymous patient pre-screening logs at each study site. Interested women will be asked to complete the validated symptom questionnaire UTI-SIQ-8^27^ and will be provided with a comprehensive patient information leaflet that details trial procedures in lay language.

The GP will exclude from participation all women with one or more of the following:

Signs of a complicated UTI (anamnesis of fever, chills or flank pain).Clinically relevant immunosuppression (ie, current use of any immunosuppressive therapy, congenital or acquired disorders of immunity).Acute or chronic functional or anatomical variations in the urinary tract except for chronic kidney failure with a glomerular filtration rate (eGFR) >45 mL/min.Permanent bladder catheter or use of bladder catheter within the past 2 weeks.UTI within the past 2 weeks.Use of any antibiotic within the past 2 weeks.Accommodation in a nursing home or hospital stay within the past 2 weeks.Severe neurologic, psychiatric illness, severe dementia or severe substance use disorder.Other severe diseases.Being unable to understand the informed consent or to complete the patient diary.Known pregnancy.

Women who consent will be asked to sign an informed consent form, which also contains data protection regulations.

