#### Control arm–usual care

Practices in the control arm will not necessarily have their management guided by POCTs. They will perform usual care. The treatment decision is usually based on symptoms. Dipsticks for detecting erythrocytes, leucocyte esterase or nitrites can be added in case of diagnostic uncertainty.^33^ Procedures are the same as those outlined above, except for POCTs: microscopy only pertains to the intervention arm.

Table 1 and figure 2 summarise trial procedures.

**Table 1 T1:** Schedule of Microscopy in Urinary Tract Infections trial procedures according to the Standard Protocol Items: Recommendations for Interventional Trials guideline^40^

Time point (day 0=patient enrolment) procedures	<0	Day 0 Baseline	Day 1–7	Day 28	End of patient enrolment*
Enrolment:					
Practice recruitment	X				
Randomisation	X				
Allocation	X				
Training	X				
Screening for potential inclusion		X			
Formal eligibility assessment		X			
Intervention:					
Baseline consultation†		X			
POCTs‡		X			
Urine sent to laboratory†		X			
Assessments:					
Practice size	X				
Paper-based CRF§		X			
Patient diary¶			X		
Follow-up telephone calls				X	
EMR review**					X

*End of patient enrolment in each practice.

†Applies to intervention and control arm practices.

‡Applies only to intervention arm practices.

§In case of reconsultation for UTI on days 1–28, paper-based follow-up CRFs are used.

¶Follow-up on days 1–7 or up to day 14 if symptoms last longer or recur.

**Follow-up on days 1–28 (CRF completeness and accuracy check).

CRF, case report form; EMR, electronic medical records; POCT, point-of-care test; UTI, urinary tract infection.

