#### Statistical analyses

Descriptive statistics will be calculated for all variables per site and as summary measures across sites. Continuous and count variables will be summarised by mean and SD, or median and IQR in case of skewed data. Binary and categorical variables will be summarised through counts and percentages. CIs and prediction intervals will be calculated for the two feasibility endpoints (recruitment efficacy and percentage of retention in the trial) in addition.

We acknowledge that this feasibility RCT is not powered to detect any statistically significant effects. Nevertheless, explorative analyses will be undertaken at the cluster-level and the individual-level to evaluate the effects of the intervention on the secondary outcome variables using two-sample hypothesis tests, random effects models and generalised estimation equations, as appropriate. Alongside point-estimates, p values and 95% CIs will be reported.

Missing data will be explored to understand why they are unavailable; when missing data are due to incomplete follow-up survival or censored regression analyses will be considered, otherwise multiple imputation with chained equations or Bayesian imputation will be applied. The intraclass correlation coefficient will be calculated for the secondary endpoints to inform subsequent sample size and power calculations.

All the analyses will be undertaken using statistical software packages Stan,^36^ R and Stata (StataCorp College Station, Texas, USA: StataCorp).

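### The symptom-burden AUC includes a pre-intervention score and baseline adjustment is not specified; adjusting for baseline UTI-SIQ-8 is a free improvement under open post-allocation recruitment

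*Protocol article*

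**What the plan says.** Under Secondary objectives, the protocol article lists "Total symptom burden on days 0–7 (area under the curve of the UTI-SIQ-8 total symptom score").

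Table 1 (under Control arm–usual care) fixes the clock: "Time point (day 0=patient enrolment) procedures". Its footnote schedules the diary as "Follow-up on days 1–7 or up to day 14 if symptoms last longer or recur". The diary therefore supplies days 1 to 7.

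The only UTI-SIQ-8 completion described for day 0 is at presentation (Identification of women eligible for inclusion): "Interested women will be asked to complete the validated symptom questionnaire UTI-SIQ-8". That step is described ahead of GP exclusion and consent, and so ahead of the point-of-care tests and the treatment decision.

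Under Statistical analyses, intervention effects on secondary outcomes are explored at cluster and individual level "using two-sample hypothesis tests, random effects models and generalised estimation equations, as appropriate". No covariate is named and none is excluded. The same section says that the trial is not powered for effects, although p values and 95% CIs will be reported.

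On allocation, "practice size will be balanced between the two arms (each with 10 practices) using minimisation" (Randomisation of study sites). The strengths and limitations list warns that "post-randomisation recruitment may represent a source of selection bias".

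**The concern.** A score taken before the intervention carries no information about its effect, yet here it is part of the outcome. In an individually randomised, concealed trial this would add only noise. Here the practices already know their arm when staff approach women and women decide whether to consent. If one arm enrols women with milder or more severe symptoms, the difference enters the AUC twice: directly through day 0, and indirectly because later scores track the first one.

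One of the listed methods, the plain two-sample test, cannot remove that difference. Random effects models and GEE can, but only if the baseline score is put into them, and the article leaves the choice open.

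Symptom burden is one of the outcomes that bear on whether antibiotics can be reduced safely, which the Abstract gives as the question behind the pilot. A biased or needlessly imprecise estimate would be a poorer guide for the later trial.

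**Working it through.** The article gives no planning figure for this outcome. Its one precision statement (Sample size considerations) concerns retention and does not bear on this point.

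**Inputs from the article:** 20 practices, 10 per arm, 10 women per practice on average, so 100 per arm; AUC window days 0–7; diary days 1–7.

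**Assumptions, not in the article:** trapezoid rule on daily scores; equal SD on each day; correlation *r* between baseline and each later day; ICC; size of any recruitment difference.

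**1. Weight of day 0.** Trapezoid weights for days 0 to 7 are 0.5, 1, 1, 1, 1, 1, 1, 0.5, which sum to 7. Day 0 carries 0.5/7 = 7.1%. If daily scores are simply summed, it carries 1/8 = 12.5%.

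**2. Effect of a baseline difference of 1 SD.**
- AUC 0–7 shifts by 0.5 + 6.5*r*: 2.45 for *r* = 0.3 and 3.75 for *r* = 0.5.
- The direct day-0 share is 0.5/2.45 = 20% and 0.5/3.75 = 13%.
- AUC 1–7 (weights sum to 6) shifts by 6*r*: 1.8 and 3.0.
- Per day of window, the shift is 2.45/7 = 0.35 against 1.8/6 = 0.30, and 3.75/7 = 0.54 against 3.0/6 = 0.50.

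Moving the start to day 1 therefore leaves most of the shift in place.

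**3. Chance imbalance.** The SD of the baseline difference between arms, in SD units, is √[(2/100)(1 + 9·ICC)]: 0.14 for ICC 0, 0.17 for ICC 0.05 and 0.19 for ICC 0.10. Its mean is zero, and the standard error of an unadjusted test already covers it.

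**4. Simulation with no treatment effect.** 20 clusters of 10, ICC 0.05, a standardised outcome with correlation ρ to baseline, 4,000 runs per setting. Unadjusted: t test on cluster means (18 df). Adjusted: the same test on cluster means of residuals from a regression on baseline.

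| Recruitment difference | ρ | Unadjusted bias | Unadjusted SD | Unadjusted type I error | Adjusted bias | Adjusted SD | Adjusted type I error |
|---|---|---|---|---|---|---|---|
| none | 0.3 | 0.00 | 0.171 | 5.1% | 0.00 | 0.161 | 5.1% |
| none | 0.5 | 0.00 | 0.170 | 5.1% | 0.00 | 0.146 | 5.0% |
| none | 0.7 | 0.01 | 0.168 | 4.4% | 0.00 | 0.120 | 4.4% |
| 0.3 SD | 0.3 | 0.09 | 0.170 | 7.3% | 0.00 | 0.160 | 4.7% |
| 0.3 SD | 0.5 | 0.15 | 0.172 | 13.0% | 0.00 | 0.147 | 5.2% |
| 0.3 SD | 0.7 | 0.21 | 0.166 | 21.1% | 0.00 | 0.118 | 4.1% |

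The results follow simple formulae. Bias is 0.3ρ = 0.09, 0.15, 0.21. The adjusted SD is about 0.17·√(1 − ρ²) = 0.162, 0.147, 0.121.

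**5. Choice of window once baseline is in the model.** The day-0 term, 0.5 × baseline, is a multiple of the covariate, so it changes only the covariate's coefficient and contributes nothing to the arm difference. For summed daily scores, days 0–7 and days 1–7 then give the same arm difference. Under the trapezoid rule they differ only in the weight on day 1 (1 against 0.5).

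**The case against.** The strongest reply is that this turns silence into a defect. Two of the three named methods accept covariates, the choice among them is left open, and a covariate list for an exploratory outcome normally belongs in an analysis plan that is not shown. This stands in part. A reader might infer that baseline is excluded from the comparison, and the article does not say so. What the article does fix is an outcome window that contains a pre-intervention score, and a menu that includes an unadjusted test.

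A reader might also infer that any baseline imbalance becomes treatment effect. It does not: chance imbalance leaves the test unbiased and at its nominal level (first three rows of the table). Bias needs differential recruitment. The article also takes steps against that: sites identified before randomisation, consecutive approach, and pre-screening logs. These reduce the risk but cannot exclude it, since consent still follows allocation.

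Nor is the day-0 start the main fault, as steps 1 and 2 show.

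Nor does leaving out practice size create bias. Minimisation balances it, and the article's reason for using it is recruitment capacity, with no stated link to symptoms.

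Finally, the stakes are limited. The feasibility rule under Primary objective uses only recruitment and retention.

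**Conclusion.** The point holds as a free improvement. The outcome includes a score taken before the intervention, the comparison may be run unadjusted, and the article itself names the recruitment mechanism that could make baseline differences systematic.

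Under the assumptions above, a 0.3 SD recruitment difference would bias an unadjusted comparison by 0.09 to 0.21 SD and raise type I error to between 7% and 21%. With no such difference the gain is precision only: the variance falls by roughly ρ², that is 9% to 49% for ρ of 0.3 to 0.7.

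The correlations, the ICC, the 0.3 SD difference and the trapezoid rule are not in the article. The simulation also lets all differential selection act through the measured baseline score, so the zero adjusted bias is a best case; selection on unmeasured factors would remain. The endpoint is secondary and exploratory, and no stated decision rests on it.

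**What to change.** State that arms are compared on symptom burden in the random effects model or GEE already named, with baseline UTI-SIQ-8 total score as a linear covariate, in place of an unadjusted two-sample test. For a cluster-level analysis, use the two-stage version: regress the individual AUC on baseline, then compare the 20 practice means of the residuals.

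Define the AUC over days 1–7, or keep days 0–7. With the covariate in the model, the day-0 score no longer affects the arm difference. Say which window and which rule (trapezoid or sum) is used.

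Practice size may be added as an optional precision covariate.

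The cost is a change of analysis wording and one regression coefficient. The score is already collected at presentation, so there is no extra burden on patients or practices. The article reports recruitment as ongoing, so the wording can be settled before outcomes are compared.
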